### Outputs

The information obtained about the ICC and effect size will make it possible to determine the sample size required for a definitive, larger-scale trial. In addition, this initial RCT will supply additional information about the new measure, provide an opportunity to test the intervention in a systematic way, and allow us to gain a clear picture of the practicalities involved in implementing the research method in the care homes. Findings will be incorporated into existing training provision for care staff offered by the Bangor Dementia Services Development Centre and the Bradford Dementia Group.

## Discussion

There is evidence to suggest that awareness at the level of sensory and perceptual responses can be observed even in people with very severe or end-stage dementia, and that the extent to which this awareness can be expressed or identified is influenced by the context and the nature of the caregiving interactions involved [41]. This study will provide an accessible, user-friendly tool that care staff can use to structure their observations of residents' awareness in the course of their daily work. Care staff participating in the intervention in Stage 3 of the study will be given the opportunity to focus on, observe, and discuss the way in which residents with severe dementia can demonstrate awareness, using this tool. The experience they gain is expected to assist them in providing sensitive, high-quality care, with beneficial effects on the quality of life of residents. Stage 3 of the study will offer preliminary evidence regarding this hypothesis. If the hypothesis is supported, our aim will be to develop a large-scale, multi-site RCT in order to provide definitive evidence about the benefits for care staff, residents and organizations of increasing the sensitivity of care staff to signs of awareness in residents with severe dementia. While such a trial is likely to present considerable methodological and practical challenges, the development of evidence-based approaches to improving quality of care and quality of life for residents with severe dementia represents an important priority.

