## Stage Three: Intervention trial

### Design

In this CRT paid carers will be trained to use the new measure of awareness and the effects on resident well-being and quality of life will be evaluated. Eight care homes will be recruited to the trial. Half the homes will be randomised to receive the training intervention; the remainder will receive no additional input. Baseline assessments will be completed in pairs of homes of similar size and type (public or independent sector) before one of the pair is randomised to receive the intervention. A CONSORT-style flowchart is shown in Figure 1.

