### Participants

Stage Three will be conducted with 8 care homes which were not involved in the previous stage. We will recruit 10 residents per home giving a total sample of 80 people with severe dementia who have no, or only very limited, verbal communication.

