### Data analysis

The data analysis will have four purposes: first, to estimate the intra-class correlations (ICC) required to power a large-scale trial; second, to conduct a confirmatory factor analysis on the developed tool in order to test the hypothesised structure which emerged from stage 2; third, to develop and test an analysis plan based on multilevel modelling; and fourth, to examine change from baseline scores on all outcome measures by randomisation group to assess possible effect size associated with both intervention and control arms (the repeated observations and ratings made by staff may trigger some changes in the control homes). A sample size of 8 care homes with 10 participants per home achieves 90% power to detect an ICC of 0.3 under the alternative hypothesis when the ICC under the null hypothesis is 0.0 using an F-test with a significance level of 0.05 [40]. The proposed sample size will also yield estimates of the standardised effect size of the change from baseline in either arm of the trial with a 95% confidence interval of +/- 0.3.

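### The pilot's effect estimate is to help size the definitive trial and bears on whether it follows, but 4 versus 4 homes estimates that effect too imprecisely for either use

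*Protocol article*

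**What the plan says.** Three places in the protocol article bear on this.

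- **Stage Three, Outputs:** "The information obtained about the ICC and effect size will make it possible to determine the sample size required for a definitive, larger-scale trial". The effect size is thus named beside the ICC as an input to the next trial's size.
- **Discussion:** Stage Three is described as giving preliminary evidence on the hypothesis of benefit, followed by "If the hypothesis is supported, our aim will be to develop a large-scale, multi-site RCT in order to provide definitive evidence". No definition of *supported*, threshold or lead outcome is attached.
- **Stage Three, Data analysis:** the sample size has two justifications. One, resting on an F-test at the 5% level, is that it "achieves 90% power to detect an ICC of 0.3 under the alternative hypothesis when the ICC under the null hypothesis is 0.0". The other is that it estimates the "standardised effect size of the change from baseline in either arm of the trial with a 95% confidence interval of +/- 0.3". Neither concerns the difference between arms.

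On the design: "We will recruit 10 residents per home giving a total sample of 80 people with severe dementia" (Participants) and "Half the homes will be randomised to receive the training intervention; the remainder will receive no additional input" (Design). That gives four homes and 40 residents per arm. Homes are paired by size and type before randomisation.

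**The concern.** The benefit hypothesis is about the difference between trained and untrained homes. The article gives neither power nor precision for that difference, yet it intends the effect estimate to help size the definitive trial and, in some unstated way, to bear on whether that trial follows.

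Required sample size varies with the inverse square of the assumed effect, so an imprecise estimate gives a very unstable sample size. If the same estimate also has to look favourable before anyone proceeds, the estimates that survive are on average too large, and the trials sized on them too small. What is at stake is an underpowered definitive trial in a population that is hard to recruit and study.

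**Working it through.** **Inputs from the article:** 8 homes, 10 residents each, 1:1 allocation; ICC 0.3 as the detection target.

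**Assumptions:** ICCs of 0.05 and 0.1; true between-arm benefit of 0.5 SD, in units of the SD of the analysed score; two-sided 5% for the arm comparison; no dropout; pairing ignored (6 df).

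**1. The article's own figures.**
- ICC test: P(F(7,72) > Fcrit / (1 + 10×0.3/0.7)) = 0.896, against the stated 90%. Reproduced.
- Within-arm interval: 1.96/√40 = 0.310, against the stated 0.3. Reproduced, but only for one arm with 40 residents treated as independent. At ICC 0.3 the design effect is 1 + 9×0.3 = 3.7, and the half-width becomes 1.96×√(3.7/40) = 0.60.

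**2. Precision and power for the between-arm difference.** SE = √(2×(1 + 9×ICC)/40). Half-width = 2.447×SE. Power is from the noncentral t on 6 df.

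| ICC | SE | 95% half-width (SD) | Power at 0.5 SD | Effect detectable with 80% power (SD) |
|---|---|---|---|---|
| 0.05 | 0.269 | 0.66 | 35% | 0.91 |
| 0.1 | 0.308 | 0.75 | 28% | 1.04 |
| 0.3 | 0.430 | 1.05 | 17% | 1.45 |

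Even at ICC 0 the half-width is 0.55 and the power 47%. If the pairs are analysed, only 3 df remain. With no allowance for any variance that pairing removes, the half-width is then 0.86 to 1.37 over ICC 0.05 to 0.3.

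**3. What that does to sizing.** Residents per arm for 90% power, before any design effect, are 526, 234, 85 and 33 for effects of 0.2, 0.3, 0.5 and 0.8 SD. An interval centred on 0.5 with half-width 0.66 runs from −0.16 to 1.16, wider than that whole range.

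**4. Main trial sized on the estimate, if any favourable estimate leads on.** True power is Φ(3.2415×0.5/estimate − 1.96). It falls below 80% when the estimate exceeds 0.5×3.2415/2.8016 = 0.579. With the estimate normal about 0.5:

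| ICC | P(estimate > 0) | P(estimate > 0.579) | Share of main trials under 80% power |
|---|---|---|---|
| 0.05 | 0.968 | 0.385 | 0.385/0.968 = 40% |
| 0.1 | 0.948 | 0.399 | 0.399/0.948 = 42% |
| 0.3 | 0.877 | 0.428 | 0.428/0.877 = 49% |

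**5. The same, if *supported* means p<0.05 in favour of the intervention** (simulation, same SEs, 6 df):

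| ICC | Chance of proceeding | Mean estimate when proceeding (SD) | Mean true power of main trial |
|---|---|---|---|
| 0.05 | 35% | 0.74 | 62% |
| 0.1 | 28% | 0.81 | 55% |
| 0.3 | 17% | 1.04 | 39% |

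**6. An intermediate reading, estimate above 0.3 SD:** the mean estimate when proceeding is 0.61 to 0.73 SD, and mean main-trial power 76% to 66%, over ICC 0.05 to 0.3.

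**The case against.** The strongest reply is that the article has no progression rule. The conditional sentence is one forward-looking statement of an aim, placed after the Stage Three evidence has been called preliminary. The four listed purposes of the analysis do not include a test of efficacy. The Abstract says, without condition, that results will inform the design of a larger trial.

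This stands, and it limits the point. A reader might infer that a worthwhile intervention would usually be abandoned. That follows only if *supported* means statistical significance, which the article never says. If any favourable estimate suffices, the chance of proceeding with a true 0.5 SD benefit is 97%, 95% or 88% at ICC 0.05, 0.1 or 0.3. The mean estimate among those proceeding is then only 0.52, 0.53 or 0.60 SD, and a trial sized on that mean would have 88%, 86% or 77% power. A reader might likewise take a pilot estimate of 0.8 SD for a true 0.5 as typical; it gives 53% main-trial power. Without a significance filter, an estimate that large or larger arises only 13%, 17% or 24% of the time.

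It can also be said that the inputs are partly assumed, that pairing may recover some precision, that the hypothesis spans several outcomes, and that sizing belongs to the next trial's own protocol. The first three are fair and are the reason for showing ranges. The last does not dispose of the matter: the Outputs section says positively that the effect size will serve for sizing, so this is not something merely left to a fuller document.

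**Conclusion.** The point holds for sizing on every reading of *supported* examined. The between-arm interval is about ±0.66 to ±1.05 SD, too wide for the estimate to size a definitive trial. For a true benefit of 0.5 SD, between 40% and 49% of main trials sized on any favourable estimate for 90% power would have under 80% true power. Under a significance criterion, mean main-trial power would be 62% to 39%, with a 35% to 17% chance of reaching that stage.

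For progression the point is narrower. The article ties its aim of a larger trial to support for a hypothesis that the pilot is not sized to test, and leaves *supported* undefined. It does not lay down a formal go/no-go test, and frequent abandonment of a useful intervention cannot be read out of it.

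The figures rest on ICCs of 0.05 and 0.1 and a true effect of 0.5 SD, none of them in the article, and on ICC 0.3, which appears there only as a detection target. They also assume a two-sided 5% level, 6 df and no dropout. The change is worth making, but nothing in this trial's allocation, conduct or data collection is affected.

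**What to change.** **Stage Three, Outputs.** State that the definitive trial will be sized on a pre-stated minimum important difference. Take from this trial the SD, the correlation between baseline and follow-up, the ICC with its confidence interval, attrition and cluster size, but not the observed effect.

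**Discussion.** Replace the condition that the hypothesis be supported. Progression would rest on the practicality of delivering the intervention and of the research procedures, unless the 95% interval for the between-arm difference excludes the minimum important difference. The Outputs section refers to practicalities only in general terms, so the team must set the specific criteria.

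**Cost.** Two wording changes and agreement on a minimum important difference for a lead outcome. The stopping clause will seldom bite: with a half-width of 0.66 and a minimum important difference of, say, 0.5 SD, the estimate would have to fall below 0.5 − 0.66 = −0.16 SD. That reflects what eight homes can show.
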